**Rationale for Lifestyle Change interventions**

Youth are immersed in social media and doing little physical activity – poor lifestyle choices that impact their physical and mental health. Reviewing 102 health records of youth (50♀) receiving specialist support at CHEO we found few met criteria for major psychiatric diagnoses. Nevertheless, during the first two visits over 90% were counselled about changing sleep, physical activity and/or screen time. That mental health specialists are addressing the need for lifestyle change in the first visits with virtually all adolescents is evidence of the importance of lifestyle behaviour assessment/change as part of mental health treatment. There is a need to study lifestyle change intervention effectiveness in youth with mental illness because such interventions offer affordable, enjoyable, rewarding, and stigma-free treatment options that have no/few side effects/complications, and can be done individually or with family^14^. Healthy behaviours and moods spread through social networks, providing an opportunity for multiplier effects of lifestyle change on other family members, friends and neighbours^23^.

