## Study Objectives

This study will evaluate the efficacy of 6 months of HELP e-intervention access with kinesiologist support in a randomized controlled trial to determine if the changes in emotional health (primary outcome) and lifestyle behaviours (secondary outcomes) differ from changes among youth with delayed intervention access (control condition). Sustainability of the intervention will be assessed for an additional 6 months. Participants will be youth 12-17 years of age who contact youth mental health services (1Call1Click). We will also evaluate the impact of the HELP e-intervention on the use of mental healthcare services, the need for mental health professional support of lifestyle behaviours and the association between self-reported and objectively measured lifestyle behaviours.

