# Eligibility Criteria

## Inclusion Criteria

Participants will be eligible for this study if they are 12-17 years of age when they are seeking, waiting for or receiving support for emotional distress. To be included in the study, youth must be: a) able to provide informed consent to study participation, b) able to engage in the HELP e-intervention in English (French translation of the e-modules will not be available until intervention efficacy is established), c) willing to be randomized to a study group, d) willing to complete objective behaviour measures if selected (1 of 3 participants), e) willing to complete the study questionnaires, and f) willing to provide consent for evaluation of mental healthcare system outcomes via their health record.

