## Study Procedures/Evaluations

### Recruitment

The primary avenue for recruitment will be via 1Call1Click. During our pilot study of the HELP e-intervention (REB #21 85X) we developed a best practice advisory flag within EPIC (Appendix A) that was provided to 1Call1Click intake staff if the youth met the age criteria for the research study. Youth who access 1Call1Click have an initial assessment by intake staff. Staff have information about the research study and have been educated regarding the inclusion/exclusion criteria. If the research study could be appropriate for the patient, the intake staff will ask the patient/family if they would like more information about research. If the response is positive, intake staff will send an EPIC inbasket message to the research team who will follow up with the patient/family to discuss the study details.

During the pilot study we also received feedback from youth, families and clinicians requesting that the HELP e-intervention be more widely available to youth who are at various stages in their journey to mental wellness. Therefore, additional youth may be recruited through our two secondary recruitment options. CHEO mental health clinicians will be able to refer youth for enrollment in the research study if they have obtained permission from the youth to do so. This avenue for recruitment will enable youth on the wait list for specialist support or who are currently receiving CHEO support to be eligible for study recruitment. We will also distribute the study information via posters (Appendix B) and social media posts (Appendix C) in CHEO patient areas and through our youth partner groups (CHEO Youth Forum, CHEO-RI Family Leader Program, YouthNet / R$é$seau Ado, the study’s Lived Experience Advisory Group, etc.). Youth who contact the research team after viewing the study information will also be eligible to enroll.

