### Study Assessments

A researcher blinded to study group allocation will work with enrolled youth to complete all study assessments. The accurate/reliable study questionnaires include measures of emotional strength (Strengths and Difficulties Questionnaire)^34^, lifestyle choices (Youth Quality of Life-short form)^35^, readiness for behaviour change (Stages of Change Questionnaire^36^), and sleep (Adolescent Sleep Hygiene Scale)^37^, physical activity (Habitual Activity Estimation Scale)^38^, and leisure screen time (Adolescent Sedentary Activity Questionnaire)^39^ behaviours. All enrolled youth will complete all questionnaires at 0, 3, 6 and 12 months. As in our pilot study (REB #21 85X), the questionnaires (Appendix E) will be completed virtually using RedCAP, with automated scoring of the responses according to published methods. At each assessment, youth will be asked to voluntarily self-report age (years), gender (boy, girl, unkown, other, prefer not to answer), and their use of other mental health therapies (Appendix F). Study enrollment does not restrict access to or use of other mental health supports.

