# Statistical Plan

## Sample Size Determination

The size of the study sample will be determined by the number of eligible youth contacts (with 1Call1Click or directly to the research team). Our pilot study approached 5-10 youth/week via 1Call1Click with 25% enrolling, providing an expected 400-800 potential and ~100-200 enrolled participants over 18 recruitment months. Complete data for 122 youth would provide 80% power to detect a 3.4 point difference in emotional health (Strengths & Difficulties Questionnaire), equivalent to the 19.5% improvement observed in our 3-month pilot study.

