### Efficacy Outcomes

The primary outcome is youth emotional well-being as measured by the Strengths & Difficulties Questionnaire (SDQ^34^). We define a clinically significant improvement as a score decrease of 15%, with the reduction occurring only when participants have engaged with the intervention. This change is just less than 1/2 of the SDQ improvement observed after 6 months of specialist community mental health services^43^. We do not expect HELP benefits to be equivalent to traditional mental health interventions. However, we believe that the ability to improve emotional health half as well as traditional therapies would provide a meaningful and important change. In our pilot study, SDQ scores improved by 19.5% in 3 months among engaged youth. We will evaluate the change in SDQ from baseline to 6 months in a repeated measures model adjusted for age (years), gender, intervention adherence, type of mental health concern (e.g., anxiety, depression, etc. as documented during 1Call1Click intake), and support referral (community or specialist services recommended by 1Call1Click intake staff). The impact of sex will be investigated if participants include a sufficient number of youth who do not identify as the gender aligned with their sex.

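### Care status at entry is left out of the fixed covariate list, although youth already in treatment are eligible and the information is collected at baseline

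*Protocol*

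**What the plan says.** **Population.** Study Objectives describes the sample by one entry route: "Participants will be youth 12-17 years of age who contact youth mental health services (1Call1Click"). Inclusion Criteria is broader: "12-17 years of age when they are seeking, waiting for or receiving support for emotional distress". Recruitment makes 1Call1Click the primary avenue and adds two secondary ones, clinician referral and posters or social media. Referral is said to allow "youth on the wait list for specialist support or who are currently receiving CHEO support to be eligible for study recruitment".

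**Model.** Efficacy Outcomes fixes the adjusters for the primary SDQ model as age, gender, intervention adherence, and "type of mental health concern (e.g., anxiety, depression, etc. as documented during 1Call1Click intake), and support referral (community or specialist services recommended by 1Call1Click intake". The same section later applies this list to all efficacy models.

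**Data on care.** Study Assessments has youth voluntarily report, at every assessment, age, gender "and their use of other mental health therapies (Appendix F). Study enrollment does not restrict access to or use of other mental health supports".

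**What care may do.** Efficacy Outcomes sets a 15% fall in SDQ as clinically significant and adds: "This change is just less than 1/2 of the SDQ improvement observed after 6 months of specialist community mental health services". The rationale section reports, from a review of 102 records of youth in specialist care, that "during the first two visits over 90% were counselled about changing sleep, physical activity and/or screen time".

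**Sizing.** "Complete data for 122 youth would provide 80% power to detect a 3.4 point difference in emotional health". This is equated with the 19.5% improvement seen in the pilot. No SD is given.

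**The concern.** Youth who enter while in treatment may follow a different SDQ course over six months from youth who are still seeking or waiting for it. If so, care status at entry explains part of the outcome variance. Leaving it out of the model leaves that variance in the error term.

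The listed term closest to it, support referral, does not stand in for it. It records what intake staff recommended, not what the youth is receiving. The protocol's background cites waits of 8-30 months, so a youth referred to specialist services may receive nothing in months 0-6. Both care-related terms are also defined by 1Call1Click intake, whereas referral by a clinician is the route named for youth already in CHEO care.

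This cannot be put down to detail deferred to an analysis plan, because the protocol itself fixes the list and applies it to all efficacy models. At stake is some precision in the primary comparison, and a clear statement of the population to which the result applies.

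**Working it through.** **Inputs from the protocol:** N = 122 with complete data, 80% power, difference 3.4 points = 19.5%, significance level 0.05, clinically significant change 15% and just less than half of the specialist-care improvement.

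**Assumptions (not in the protocol):** two-sided test; 1:1 allocation (61 per arm); share s in care at entry of 20%, 30% or 50%; prognostic gap g between youth in care and the others of 2.6 or 5.2 points.

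**1. The plan's own figure.** With no SD stated, 122 cannot be reproduced independently. Solving backwards with the t-test, 61 per arm and 80% power need a standardised difference of 0.511, so SD = 3.4 / 0.511 = 6.65 (6.70 by the normal approximation). With that SD, 122 is coherent.

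**2. Scale of the gap.**
- Implied baseline SDQ: 3.4 / 0.195 = 17.4.
- Implied improvement under specialist care: 15% is just less than half, so just over 30%. 0.30 × 17.4 = 5.2 points.
- Half of that: 0.15 × 17.4 = 2.6 points.

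The 5.2-point gap is an upper-end case. It supposes that youth in care improve by the full amount and that the others do not change.

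**3. Gain if 6.65 is the total SD.** Share of variance explained: R² = s(1−s)g² / SD². Adjusted SD = 6.65 × √(1−R²). Power is at 3.4 points with 61 per arm.

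| g | s | R² | Adjusted SD | Power |
| --- | --- | --- | --- | --- |
| 2.6 | 20% | 0.025 | 6.57 | 81.0% |
| 2.6 | 30% | 0.033 | 6.54 | 81.3% |
| 2.6 | 50% | 0.039 | 6.52 | 81.5% |
| 5.2 | 20% | 0.099 | 6.31 | 83.9% |
| 5.2 | 30% | 0.130 | 6.20 | 85.2% |
| 5.2 | 50% | 0.155 | 6.11 | 86.2% |

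Example: 0.2 × 0.8 × 5.23² / 6.65² = 0.099. The degree of freedom spent on the covariate makes no visible difference to these powers.

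**4. The other reading of the SD.** If the back-solved SD (6.70, normal approximation) were the SD within care strata, the total SD without the covariate would be √(6.70² + s(1−s)g²). At g = 5.2 this is 7.02 for s = 20% and 7.19 for s = 50%. Power would be 76.2% and 74.2%, and the covariate would restore 80%. The protocol does not say which reading applies. Under either, the covariate is worth about 1 to 6 power points.

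**The case against.** **The effect is diluted.** A reader might infer that HELP must do less for youth already counselled on the same behaviours, so that the average effect falls below 3.4 points. The documents do not support this. Care open to both arms does not in itself shrink the difference between them. Dilution needs a smaller HELP effect among youth in care, and no figure for that is given. The protocol also says HELP is not an education intervention, and suggests that lifestyle change may help youth take part in treatment, which could point the other way. A main-effect covariate would not cure dilution in any case.

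**The contrast is biased by imbalance.** With 20-50% in care, 95% limits for a chance imbalance are 1.96 × √(2s(1−s)/61) = 14 to 18 percentage points. At a 5.2-point gap these would move the arm difference by 0.74 to 0.93 points. That looks large beside 3.4, but randomisation balances care status in expectation. These shifts are ordinary sampling error already covered by the standard error: 1.96 × 6.65 × √(2/61) = 2.36 points.

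**The trial is noisier than sized.** This cannot be shown. No SD is stated, and the pilot was itself expanded to youth receiving support, so the sizing figures may already reflect the mix.

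**The gap and share are guesses.** This stands. The 30% refers to six months of specialist community services, so applying it to youth part-way through care is an extrapolation. Youth without care at entry may also start it. Since 1Call1Click is the primary route, a 50% share is at the high end.

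These objections limit the size of the point. None gives a reason to leave out a baseline predictor that is already collected.

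**Conclusion.** The point holds as a modest gain in precision. The fixed covariate list omits a plausible baseline predictor that the trial already asks about, and the listed referral term measures something else. Under the assumptions above and the total-SD reading, adding it raises power at 3.4 points from 80% to about 81-82% for a 2.6-point gap and to 84-86% for a 5.2-point gap.

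Separately, Study Objectives describes a narrower population than Inclusion Criteria and Recruitment. The latter two agree with each other, so this is a matter of wording.

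The planned comparison remains valid without the change. Nothing in the protocol establishes bias, dilution or a shortfall against the planned power.

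**What to change.** - Add baseline care status (currently receiving or not receiving mental health treatment) as a covariate in the primary SDQ model and the other efficacy models. Take it from the baseline therapy item and fill missing values from the chart, which is reviewed anyway. Use the baseline value only, because therapy use after randomisation may itself be affected by HELP.
- Report the arm effect within each care status as a supporting estimate, labelled as imprecise. The trial is not sized for it.
- Reconcile the population sentence in Study Objectives with Inclusion Criteria and Recruitment.

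**Cost:** wording changes, one degree of freedom, and some chart checks because the item is voluntary. Appendix F is not in the text at hand, so confirm that its item separates treatment in progress at entry from past or planned treatment.

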## Data Analyses

Data cleaning will be on-going throughout data collection. Initial data analyses of youth enrolled in the first 9 months of the RCT will be completed in months 15-20. Detailed analysis syntax and modeling will be retained for use in the final modeling/analyses when data collection is complete. Statistical significance will be set at p<0.05 for all analyses.

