Secondary efficacy outcomes are measures of readiness for behaviour change (i.e., stage of change) and sleep, physical activity and screen time behaviour. Behaviour change theory emphasizes that individuals move through a series of stages, with the most effective intervention differing for each stage. HELP supports youth in all stages of change. “Learn” targets youth not yet considering behaviour change. “Pro’s and Con’s” guides youth to address their ambivalence towards change. “Goals” provide step-by-step plans so youth can act on their intention to change behaviour. “Roadblocks” support the maintenance of recent behaviour changes. Paired t-tests will examine participants’ stage of change at enrollment and 6 months to assess whether HELP enhanced their readiness for behaviour change. Modeling how the behaviour change stage differs, with adjustments for age, gender, intervention adherence, type of mental health concern and support referral, will assess whether HELP similarly impacts behaviour change among all youth. The same analyses will be completed for each behaviour outcome with stage of change at 6-months a mandatory variable as theory indicates that achieving Stages 3 to 5 is required for behaviour change to occur (Stages 1 & 2 are moving toward the decision to change behaviour).

A repeated measures model of the primary and secondary outcomes will evaluate changes between study groups, comparing changes occurring during intervention access to changes when the intervention is not available. Changes between the 0 and 6-month assessments for youth randomized to immediate intervention access and between the 6 and 12-month assessments for youth randomized to the wait list group will evaluate HELP e-intervention efficacy. Differences between the 6 and 12-month assessments for youth randomized to immediate intervention access will evaluate the sustainability of the intervention effects. Differences between the 0 and 6-month assessments for youth randomized to the wait list group will evaluate changes in study outcomes over time without the HELP e-intervention. Comparisons between 0 and 3-month and 3 and 6-month outcomes will determine the required length of the HELP e-intervention for optimal outcomes. All models will be adjusted for age, gender, intervention adherence, type of mental health concern and support referral.

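### The paired t-test on stage of change treats ordered stages as equal steps and makes no arm comparison, so alone it cannot show that HELP raised readiness or how many youth reached Stages 3 to 5

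*Protocol*

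**What the plan says.** All of this is in the protocol's Statistical Plan, under Data Analyses and its Efficacy Outcomes subsection.

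- Readiness is a named secondary outcome, listed apart from the behaviours: "Secondary efficacy outcomes are measures of readiness for behaviour change (i.e., stage of change) and sleep, physical activity and screen time behaviour".
- The test named for it is a paired t-test on "stage of change at enrollment and 6 months to assess whether HELP enhanced their readiness for behaviour change". The text does not say whether one arm or both enter the test.
- The stages are not described as interchangeable steps: "theory indicates that achieving Stages 3 to 5 is required for behaviour change to occur", whereas "Stages 1 & 2 are moving toward the decision to change behaviour".
- That distinction is given as the reason for a covariate in the behaviour models: "The same analyses will be completed for each behaviour outcome with stage of change at 6-months a mandatory variable".
- Early-stage youth are an intended audience: "HELP supports youth in all stages of change".
- The paired test is not the only analysis. Stage is also modelled with covariate adjustment, and "A repeated measures model of the primary and secondary outcomes will evaluate changes between study groups". Neither model is said to be ordinal or linear.
- The significance rule is "Statistical significance will be set at p<0.05 for all analyses".

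**The concern.** The sentence on the paired t-test has two weaknesses.

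The first is the scale. A t-test works on a mean, so a step from 1 to 2, from 2 to 3 or from 4 to 5 counts the same. The same paragraph attaches particular importance to being in Stages 3 to 5. A mean change cannot show whether anyone entered that range, and no readiness analysis reports how many did.

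The second is attribution. The stated purpose is to learn whether HELP enhanced readiness, but a paired comparison of enrolment with 6 months has no control in it. Youth seeking mental health support may change stage for other reasons, including care that the protocol leaves unrestricted. If wait-list youth are included in the paired test, it also mixes in youth who had no HELP access in that period.

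At stake is the reading of one secondary outcome. A reader told that HELP enhanced readiness could not tell whether youth had reached Stages 3 to 5, or whether the wait-list arm had moved just as much.

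**Working it through.** **Inputs.** The protocol gives no sample size, baseline distribution or expected shift for stage of change, so there is no figure of its own to reproduce. The 122 complete cases under Sample Size Determination relate to the Strengths and Difficulties Questionnaire and serve here only to set a plausible n. Assumptions: 1:1 allocation, hence 122 / 2 = 61 youth per arm; 61 youth in the paired test; two-sided p<0.05; five stages scored 1 to 5, inferred from the reference to Stages 3 to 5.

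**Formula.** For stage differences d, t = mean(d) / (s / √n), with n = 61 and 60 degrees of freedom. With u youth up one stage and v down one, mean(d) = (u − v)/61 and s² = [(u + v) − (u − v)²/61] / 60.

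**Case A: 4 youth move from Stage 1 to 2, nobody else changes.**
- mean = 4/61 = 0.0656
- s = √[(4 − 16/61)/60] = 0.2496
- t = 0.0656 / (0.2496/√61) = 2.05, p = 0.0445
- Three movers give p = 0.083. Four are enough at n = 30, 50, 61, 100 and 122 (p = 0.043 to 0.045).
- Newly at Stage 3 or above: none. Exact McNemar on that cut has no discordant pairs, p = 1.

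**Case B: 10 youth cross from 2 to 3 and 6 slip from 5 to 4.**
- mean = (10 − 6)/61 = 0.0656, the same as in Case A
- s = √[(16 − 16/61)/60] = 0.5121
- t = 0.0656 / (0.5121/√61) = 1.00, p = 0.32
- Newly at Stage 3 or above: 10 of 61, none crossing back. Exact McNemar p = 2 × 0.5^10 = 0.002.

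The two cases have an identical mean change and opposite content with respect to Stages 3 to 5.

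**Case C: no HELP effect, but 10% of youth in each arm move up one stage.** From Case A, the paired test in the HELP arm is significant whenever at least 4 of 61 move up. For a binomial count with n = 61 and probability 0.10, that has probability 0.87. Simulation (20,000 runs) agrees: the paired test is significant in 87% of runs and a between-arm t-test in 5%.

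**Case D: is unequal spacing the driver?** Suppose 30% move up and 10% down, all between Stages 1 and 2. The paired t-test is significant in about 73 to 74% of simulated trials. The Wilcoxon signed-rank test is significant in about 74% and the exact sign test in about 65%. Tests that rely less on spacing, or not at all, detect much the same movement. This case shows real net upward movement and is not evidence of a spacing fault.

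**The case against.** A reader might infer something stronger: that the protocol contradicts itself by counting moves between Stages 1 and 2 as a benefit when its own theory requires Stage 3. The documents do not support that. The outcome is readiness, and the behaviours are separate outcomes with their own analyses. Stages 1 and 2 are described as progress toward a decision, and one HELP component is aimed at youth not yet considering change. The Stage 3 to 5 statement justifies a covariate in the behaviour models and is not a success criterion for readiness. This objection stands in full.

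It is also fair that the t-test is not the only readiness analysis. An adjusted model and a between-group repeated measures model are planned. Their form is not stated and an SAP may settle it, so the spacing problem cannot be asserted for them. What remains is that the protocol does fix the paired t-test and gives it the job of assessing the HELP effect.

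The arithmetic has limits. Case A needs nobody to move down, and the exact sign test on it gives p = 0.125, so its significance is partly a small-count artefact of the t-test. Placing all the movement at chosen stages is illustrative, since no baseline distribution is given. Stage scoring rests on a source not at hand, and the text does not say whether there is one stage per youth or one per behaviour.

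Finally, making Stage 3 or above the outcome would be a trade-off: it would ignore intended gains from 1 to 2 and all movement within Stages 3 to 5. That rules it out as a replacement outcome but not as a supporting summary.

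**Conclusion.** The point holds in a limited form. The named test treats an ordered category as equally spaced, cannot show whether youth reached Stages 3 to 5, and cannot by itself attribute change to HELP. The attribution weakness is the larger: under equal 10% upward movement in both arms, the paired test would be significant about 87% of the time against about 5% for a between-arm test. The scale weakness is one of interpretation: the same mean change of 0.066 can go with 0 or 10 of 61 youth newly at Stage 3 or above.

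These sizes assume 61 youth per arm, two-sided testing and hypothetical patterns of movement. It is not an internal contradiction, and it does not touch the primary outcome. It concerns one secondary outcome for which between-group modelling is already planned.

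**What to change.** In Efficacy Outcomes, replace the paired t-test on stage of change with a between-arm comparison: an ordinal (for example proportional-odds) model of stage at month 6, HELP versus wait-list, adjusted for baseline stage. This respects the ordering without equal spacing and keeps credit for moves from Stage 1 to 2. Beside it, report the number and proportion at Stage 3 or above by arm at enrolment and month 6, labelled as a supporting summary and not as a replacement outcome. State also that the between-group repeated measures model, where it is applied to stage of change, will use an ordinal form.

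The cost is protocol wording and minor analysis work. No new data, visits or participants are needed. The ordinal model brings its own assumption of a common odds ratio across cut-points, which the by-arm summary helps the reader to judge.

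### An adjustment-only model of stage of change and behaviour cannot assess whether HELP works similarly in all youth; that needs study-group-by-covariate interactions

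*Protocol*

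**What the plan says.** The second part of Efficacy Outcomes in the protocol deals with the secondary outcomes. It starts with paired t-tests of "stage of change at enrollment and 6 months to assess whether HELP enhanced their readiness for behaviour change". The next step is described as "Modeling how the behaviour change stage differs, with adjustments for age, gender, intervention adherence, type of mental health concern and support referral", and the protocol says that this step "will assess whether HELP similarly impacts behaviour change among all youth".

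The approach is then carried over to sleep, physical activity and screen time: "The same analyses will be completed for each behaviour outcome with stage of change at 6-months a mandatory variable".

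A separate repeated measures model "will evaluate changes between study groups, comparing changes occurring during intervention access to changes when the intervention is not available". Its covariates have the same role: "All models will be adjusted for age, gender, intervention adherence, type of mental health concern and support referral".

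No efficacy analysis names an interaction of any covariate with study group or HELP access. The review by age group, sex and type of treatment under Healthcare System Outcomes concerns the content of chart notes, not the effect of HELP. The only significance criterion is general: "Statistical significance will be set at p<0.05 for all analyses".

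**The concern.** The question posed is whether the effect of HELP is the same for different kinds of youth. The model attached to it lists the characteristics of those youth only as adjustments. An additive model has a single HELP coefficient shared by everyone, so it assumes the similarity it is meant to assess. The remaining coefficients, for age, gender, concern and referral, describe the outcome rather than the HELP effect.

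The answer bears on who HELP is for. The protocol presents HELP as suitable for youth in every stage of change and recruits at intake, from the wait list and from current care. A covariate term read as an answer to the stated question could suggest that HELP works differently when some youth simply change more on their own. It could also miss a group that does not benefit.

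**Working it through.** **Inputs.** The protocol gives 122 complete cases (Sample Size Determination) and a 0.05 significance level (Data Analyses), taken here as two-sided. It gives no SD for stage of change or the behaviours, no allocation ratio and no subgroup sizes. Assumed for illustration: 1:1 arms, one binary characteristic split 50/50, SD 1 at each visit and a 0-6 month correlation of 0.5. The SD of change is then sqrt(2 × (1 − 0.5)) = 1. The protocol has no figure of its own to reproduce on this point.

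**Step 1: what each model tests.** Let T be study group and G the characteristic.
- Adjusted model: Y = b0 + b1·T + b2·G + error. The HELP effect is b1 in both subgroups by construction. The test of b2 asks whether Y differs by G, averaged over arms.
- Interaction model: Y = b0 + b1·T + b2·G + b3·T·G + error. The HELP effect is b1 when G = 0 and b1 + b3 when G = 1. Similar impact is a statement about b3, which the adjusted model does not contain.

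**Step 2: change as outcome, natural change differing by 0.5 SD, HELP effect equal (b3 = 0).**
- Both arms: SE(b2) = 2/sqrt(122) = 0.181, and 0.5/0.181 = 2.76. The chance of p<0.05 is Φ(2.76 − 1.96) = 79% by the normal approximation, and about 78% in simulation.
- HELP arm only: SE = 2/sqrt(61) = 0.256, and 0.5/0.256 = 1.95. The approximation gives Φ(1.95 − 1.96) = 50%, and simulation about 48%.
- Interaction test: about 5%, as it should be.

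**Step 3: change as outcome, subgroups differing only in baseline level, HELP effect equal.** The baseline difference cancels on subtraction. The covariate term is significant in about 6% of trials, close to nominal.

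**Step 4: 6-month level as outcome.** With levels 0.5 SD apart and an equal HELP effect, the covariate term is significant in about 78% of trials. With HELP effects of 1.0 and 0 SD and an untreated offset of −0.5 SD that exactly cancels the average difference, it is significant in about 4%, while the interaction is detected in about 79%. With change as the outcome and that offset already present at baseline, the 4% becomes about 76%.

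**Step 5: what the right test can do.** SE(b3) = 4/sqrt(122) = 0.362. For a 0.5-SD difference in HELP effect, 0.5/0.362 = 1.38, and power is Φ(1.38 − 1.96) = 28%. Such a difference would be missed about 72% of the time, so a non-significant interaction would not show similarity.

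**The case against.** The strongest reply is that the protocol gives no model equation. Because the sentence follows a paired comparison of enrolment and 6 months, it is naturally read as a model of change. In such a model, covariate terms do show who changes more, and baseline differences drop out (Step 3). This stands. It means that a reader should not infer that older youth who merely sit at a different stage would necessarily produce a false signal: the 78% in Step 4 holds only for a level model. The 4% there also needs an exactly cancelling offset; without it, even the level model gives about 77%. What the reply does not remove is Step 2. Change that occurs for reasons other than HELP is not netted against the wait list by a covariate main effect.

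A reader might also infer that the plan concludes the effect is similar, or will treat p>0.05 as proof of similarity. The protocol supports neither: it says only that the model will assess the question, and its significance statement is generic.

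Finally, interaction terms for secondary outcomes are often left to a statistical analysis plan. That would answer a mere omission. Here the protocol itself ties this inference to a named set of adjustments, so the sentence is wrong as it stands. It is fair that none of the six research questions concerns differences in effect between youth, which limits the weight of the point.

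**Conclusion.** The point holds in this form: the described model does not test whether the HELP effect is similar across youth, for stage of change or for the three behaviours. How misleading its covariate terms would be depends on the model used and on how youth change without HELP. Under the assumptions above, with change as outcome, false signals range from about 6% (baseline differences only) to about 78% (natural change differing by 0.5 SD; about 48% within the HELP arm alone). These figures are illustrations, since the protocol gives neither SDs nor subgroup sizes.

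The point concerns secondary outcomes only. It should not be read as a criticism of the primary SDQ analysis, to which the protocol does not attach this inference. It should be corrected, but it does not threaten the trial's main result.

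**What to change.** Replace the sentence in Efficacy Outcomes with:

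> Whether the HELP effect differs between youth will be explored on the randomised 0-6 month comparison by adding, one at a time, the interaction of study group with age, gender, type of mental health concern and support referral, in models that do not adjust for intervention adherence or 6-month stage of change. Each will be reported as a difference in HELP effect with its 95% CI, and a non-significant interaction will not be reported as a similar effect.

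Apply the same wording to each behaviour outcome. Adherence and 6-month stage are left out because both arise after randomisation and may themselves be changed by HELP; adjusting for them would mean that the interaction no longer describes a difference in the total HELP effect.

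The cost is a short change of wording and a few extra model terms on data already planned. The downside is a weaker, exploratory claim with wide intervals in place of a statement about all youth.
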